**Methods:**

This randomized controlled trial will test whether a 12-week virtual nutrition and teaching kitchen program improves diet quality (Healthy Eating Index [HEI]), compared with time- and attention-matched contact-control group. We plan to enroll 180 Veterans *≥* 65 years of age with mobility limitations who will be randomized to an intervention or control group. Participants in the intervention group will attend one live, one-hour virtual session each week for 12 weeks, including cooking demonstrations, and tailored nutrition education, with adaptive equipment and occupational therapy guidance provided as needed. Control participants will attend matched group health education sessions focused on healthy aging. Outcome assessments occur at baseline, 3 months, and 6 months. The primary outcome is change in HEI score from baseline to 3 months. Secondary outcomes include change in HEI from 3 to 6 months, and changes in social isolation, loneliness, and health-related quality of life, physical function, body composition, and fear of falling from baseline to 3 months. Sample size calculations indicate that 73 participants per group will provide 80% power to detect a 5.5-point between-group difference in HEI, allowing for 20% attrition.

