## Methods

### Study design and setting

We anticipate that this two arm, parallel randomized controlled trial will be completed over ~ 8 months per participant. An overview of the study is summarized in Fig. 1.

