**Fig. 1 Fig1:**
[figure not shown]
Experimental design

The first visit will consist of a 24-hr dietary recall, functional gait assessment, and modified physical performance test (MPPT). The second visit will be at least two days later and will consist of a second 24-hr recall, health-related quality of life, fear of falling, social isolation, food literacy, and health literacy questionnaires, collection of fasting blood sample and dual-energy x-ray absorptiometry (DEXA) scan to assess body composition. A third diet recall will be completed virtually [34]. All study procedures except for the DEXA will be repeated in an identical pattern at 3 months and 6 months (3 months after intervention completion). DEXA scans will occur at baseline and 3 months. Participants will receive $25 upon completion of each assessment timepoint (baseline, 3-months, and 6-months). Participants in the nutrition intervention group may receive an additional $20 for participation in the follow-up focus group ($95 total). This study protocol is approved by the institutional review board of the University School of Medicine and the VA Research and Development Committee (HP 00112264, version 3, Amendment 2 (2/19/2026)). The study is registered at *ClinicalTrials.gov* (NCT06726083).

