#### Virtual nutrition education + produce group

In the nutrition intervention group, 1-hour live virtual group sessions led by a trained study team member will be held weekly over 12 weeks using a HIPAA-compliant online platform.

The first part of class of each week will include the teaching kitchen cooking demonstration (~ 30 min). The remainder of the class will focus on dietary education and discussion. An overview of the nutrition and cooking skills education topics are presented in Table 2. Dietary education will review basic cooking skills, (e.g., food safety; preparation techniques such as washing fruits and vegetables) and progress to content on food selection, preparation, consuming adequate protein sources to maintain muscle mass, flavor enhancement with spices/herbs, and mindful eating. If needed, participants may also receive cooking equipment such as adaptive cooking utensils, small appliances like crock pots and/or toaster ovens/air fryers to allow participants to prepare meals in an area with a limited amount of space. Each week participants will receive an allotment of produce, similar to a community supported agriculture model [36]. In this format, participants will receive a pre-selected number of locally-grown produce items each week during the intervention provided by a local farm.

**Table 2 Tab2:** Overview of Nutrition and Cooking Skills Education Topics

- Review of food safety: good hygiene, cooking temperatures, knife safety; How to make your kitchen environment work for you.
- Proper food storage; Washing fresh produce; Reducing food waste.
- Balance/body alignment tips during food prep.
- Overview of healthy plates and food groups.
- Importance of protein for aging Veterans.
- Balancing proteins, carbohydrates & fats.
- Grocery shopping; Eating well on a budget.
- Healthy, quick breakfasts, lunches, dinners and snacks.
- Eating with mindfulness; Addressing hunger & fullness.
- Healthy recipe substitutes and modifications.
- Cooking with spices/herbs to enhance flavor.
- Home safety in the kitchen and dining spaces.

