### Outcomes

Table 3 outlines the study outcomes and timepoints of assessment.

**Table 3 Tab3:** Outcomes and Timepoints Measured

Assessment/Outcome	Baseline			Post-Intervention			Retention-Testing		
	V1	V2	V3	V1	V2	V3	V1	V2	V3
24-hr Dietary Recall/HEI	*X*	*X*	*X*	*X*	*X*	*X*	*X*	*X*	*X*
Grip Strength	*X*			*X*			*X*		
Height and Weight	*X*			*X*			*X*		
Modified Physical Performance Test	*X*			*X*			*X*		
Functional Gait Assessment	*X*			*X*			*X*		
Cooking and Food Skills Measure		*X*			*X*			*X*	
BRIEF Health Literacy Screening Tool		*X*			*X*			*X*	
USDA Adult Food Security Survey Model, 6-Item Short Form		*X*			*X*			*X*	
Lubben Social Network Scale		*X*			*X*			*X*	
Life Space Assessment		*X*			*X*			*X*	
UCLA Loneliness Scale		*X*			*X*			*X*	
PROMIS Global Health		*X*			*X*			*X*	
CHAMPS Activities Questionnaire for Older Adults		*X*			*X*			*X*	
DEXA		*X*			*X*				
Blood Draw		*X*			*X*			*X*	
Falls-Efficacy Scale-International		*X*			*X*			*X*	
Follow-up Focus Group							*X*		

Timepoints of study assessments. Each timepoint consists of 3 visits (V1, V2, V3) over a two-week period

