### Statistical methods

The primary analysis will assess within-subject change in HEI score (3-month minus baseline) using a paired samples t-test if assumptions of normality and equal variance are met. If the equal variance assumptions are violated, an unequal-variance t-test will be used. If the data are non-normal, an appropriate transformation or non-parametric alternative will be applied. Exploratory post hoc analyses will assess heterogeneity of treatment effect, with the hypothesis that dietary quality will improve in the nutrition intervention group compared to contact control. Covariates (age, race/ethnicity, sex, medical history/comorbidity, medications, education, living situation, and annual household income) will be included in negative binomial regression models, analyzing changes in outcomes from baseline to 3 months per participant. Although weight loss is not an intended outcome, we will measure how the intervention may change body composition (DEXA). The same modeling strategies (negative-binomial regression, multinomial, or linear mixed effects models) will be applied to each outcome using piecewise approach, with a change point occurring at 6 months to determine whether treatment effects differ or persist after this time. Finally, we will test whether continued participation in the virtual nutrition intervention after intervention completion moderates the persistent effect of the intervention on study endpoints. Missing data will be handled using an intention-to-treat approach with multiple imputations, with 5–10 imputations recommended to account for uncertainty in missing values and to produce valid, unbiased estimates of treatment effects [57]. No interim analysis are planned.

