This study builds upon prior work demonstrating associations between diet quality, mobility, and social isolation, but is novel in testing a virtual, interdisciplinary intervention specifically designed for older adults with mobility limitations. By integrating nutrition education, cooking skills, occupational therapy, and social engagement, this intervention addresses multiple interrelated determinants of dietary behavior that are often studied in isolation.

There are several potential barriers to implementation that warrant mention. Despite efforts to support technology access and literacy, comfort with virtual platforms may vary across participants. Health challenges, caregiving responsibility, differences in baseline cooking skills, or home environments may affect adherence. Tracking intervention adaptations using the core functions and forms framework [35] will help identify strategies to optimize adherence and scalability.

Key limitations include reliance on self-reported dietary intake, which may be subject to recall bias, and the restriction of the sample to older Veterans in a single geographic region, which may limit generalizability. Additionally, while the study includes short-term follow up (3 months post intervention), long-term sustainability of changes in dietary quality cannot be determined.

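### The piecewise persistence model puts its change point at 6 months, the last assessment, so it cannot estimate the effect it is meant to test; the break that fits the schedule is at 3 months

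*Protocol article*

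**What the plan says.** Statistical methods applies negative-binomial, multinomial or linear mixed models to each outcome "using piecewise approach, with a change point occurring at 6 months to determine whether treatment effects differ or persist after this time".

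The schedule is stated consistently elsewhere in the protocol article:

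- Abstract, Methods: "Outcome assessments occur at baseline, 3 months, and 6 months".
- Study design and setting: procedures other than DEXA are "repeated in an identical pattern at 3 months and 6 months (3 months after intervention completion". DEXA is done at baseline and 3 months only.
- Virtual nutrition education + produce group: sessions "will be held weekly over 12 weeks using a HIPAA-compliant online platform".
- Discussion, limitations: "while the study includes short-term follow up (3 months post intervention".

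The abstract lists the change in HEI from 3 to 6 months as a secondary outcome. Its other secondary outcomes run from baseline to 3 months.

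Statistical methods then adds a test of whether "continued participation in the virtual nutrition intervention after intervention completion moderates the persistent effect of the intervention".

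**The concern.** A change point is useful only if there are data on both sides of it. Here it coincides with the final visit, so the stated question, what happens to the treatment effect beyond that time, has no data behind it. The event that should divide the time axis is the end of the programme at about 3 months. A model that does not break there mixes the period in which the intervention is delivered with the period in which its effect may fade.

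At stake is the purpose of the 6-month assessment. An analyst following the text would meet an inestimable term and would have to choose another model after data are in hand. The alternative, dropping the empty term, would leave one straight line per arm.

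The participation test raises a smaller, related issue. Continued participation in the nutrition programme is not described for controls. It also arises after randomisation by the participant's own choice.

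**Working it through.** **Inputs.** Visits at 0, 3 and 6 months (abstract; Study design and setting; Table 3). Change point at 6 months (Statistical methods). Programme ends at 12 weeks. Design effect 5.5 HEI points, SD 13.3, 73 per arm, one-sided alpha 0.05 (Sample size and power).

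**The plan's own figure.** The article gives no figure for the persistence model. The 5.5 used below comes from its power statement, which reproduces: 5.5 / (13.3 × √(2/73)) = 2.498; 2.498 − 1.645 = 0.853; power = Φ(0.853) = 80.3%.

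**Step 1: can the after-change effect be estimated?** With linear segments, each arm's mean is a + b·t + c·max(0, t − k), where k is the change point. Two arms give 6 parameters.

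| Change point k | max(0, t − k) at t = 0, 3, 6 | Rank of design matrix |
|---|---|---|
| 6 months | 0, 0, 0 | 4 of 6 |
| 3 months | 0, 0, 3 | 6 of 6 |

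At k = 6 the after-change slope and its difference between arms cannot be estimated. At k = 3 both can.

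**Step 2: what remains when k = 6?** One straight line per arm. The least-squares slope over t = 0, 3, 6 is (−3·y0 + 3·y6)/18 = (y6 − y0)/6. The 3-month value drops out of the slope altogether.

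Let y be the between-arm difference. Its values at 6 months are assumptions for illustration:

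- Sustained (0, 5.5, 5.5): slope 5.5/6 = 0.917 per month; × 3 = 2.75.
- Half lost (0, 5.5, 2.75): slope 2.75/6 = 0.458; × 3 = 1.38.

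If the baseline difference is held at zero, with equal within-person correlation ρ between visits, the slope is (Σty − c·Σt·Σy)/(Σt² − c·(Σt)²), with c = ρ/(1 + 2ρ), Σt = 9 and Σt² = 45.

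- Sustained, ρ = 0: 49.5/45 = 1.1; × 3 = 3.3.
- Sustained, ρ = 0.7 (c = 0.292): (49.5 − 28.875)/(45 − 23.625) = 0.965; × 3 = 2.9.
- Half lost, ρ = 0: 33/45 = 0.733; × 3 = 2.2.
- Half lost, ρ = 0.7: (33 − 21.66)/21.375 = 0.531; × 3 = 1.6.

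| Assumed difference at 0/3/6 months | Fitted 0-3 change, baseline free | Fitted 3-month effect, baseline held at zero, ρ 0 to 0.7 |
|---|---|---|
| 0 / 5.5 / 5.5 | 2.75 | 3.3 to 2.9 |
| 0 / 5.5 / 2.75 | 1.38 | 2.2 to 1.6 |
| 0 / 5.5 / 0 | 0 | 1.1 to 0.3 |
| 0 / 5.5 / 11 | 5.5 | 5.5 |

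The true 3-month value is 5.5 in every row. Only an effect that keeps growing linearly is recovered.

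**Step 3: the participation test.** If moderation were fitted with columns 1, arm, M and arm × M, and M (continued participation) is 0 for every control, the columns M and arm × M are identical. The rank is 3 of 4 and the interaction cannot be estimated.

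**The case against.** **Could data exist beyond 6 months?** Study design and setting says the trial "will be completed over ~ 8 months per participant", but no assessment is listed after the 6-month timepoint. The note to Table 3 says "Each timepoint consists of 3 visits (V1, V2, V3) over a two-week period", so the later visits of the last round belong to that same timepoint. Counting 6 months from the end of the programme would put the change point beyond all data.

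**Could the model be coded another way?** Yes. The article says only that the approach is piecewise. A step at the 6-month visit (t ≥ 6) is saturated, rank 6 of 6, and smooths nothing. This stands as a limit on the figures, which depend on linear time. It does not rescue the stated aim, because even this coding estimates nothing after 6 months.

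**Is the 3-month effect lost?** A reader might infer that the primary endpoint is distorted. The document does not support that. The primary analysis uses 3-month minus baseline HEI, and the covariate models use changes from baseline to 3 months. Neither involves the change point.

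**Is persistence unanswerable in this trial?** That also goes too far. The 3-to-6-month change in HEI is a difference between two scheduled visits and can be compared between arms directly. The modelling sentence is at fault; the data and the endpoint are intact.

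**Is the moderation test impossible?** The article does not spell out an arm-by-participation interaction; Step 3 applies only if the word moderates is read that way. Continued participation is not defined, and its definition may sit in the full protocol. An analysis within the intervention arm remains possible. What stands is that such a comparison is self-selected and is not a randomised test of moderation.

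**Conclusion.** The change point is wrong as written. It sits on the last assessment, so there are zero planned observations after it, and this follows from the schedule alone. With linear segments the model also cannot deliver the 3-to-6-month contrast that the abstract names.

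The size of the distortion is conditional. It holds only inside this model and assumes linear time, a 5.5-point effect at 3 months and an assumed 6-month effect. The fitted 0-to-3-month difference is then about 2.75 to 3.3 if the effect is sustained, and about 1.4 to 2.2 if half is lost.

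The primary test, the baseline-to-3-month models, the sample size and data collection are untouched. The point concerns a secondary analysis and should be fixed; it does not threaten the trial's main result. The participation test is a lesser matter of labelling.

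**What to change.** In Statistical methods:

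1. Move the change point to 3 months, the end of the intervention, or treat visit as categorical with arm-by-visit terms. At three nominal visit times both give six estimable mean parameters.
2. Report the between-arm difference in 3-to-6-month change, and the between-arm difference at 6 months.
3. Exclude DEXA outcomes from this model, since they have no 6-month measurement.
4. Label the continued-participation analysis a descriptive association within the intervention arm, not a test of treatment-effect moderation.

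The cost is a few sentences, carried into the statistical analysis plan if there is one. No visit, measurement or participant is added.

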### Intervention

Following baseline testing, participants will be randomized to one of two virtual intervention groups using a 1:1 ratio (nutrition intervention; *n* = 90 or contact control; *n* = 90) using blocked randomization with a 1:1 allocation ratio. Randomization is not stratified. The randomization allocation, generated by the study statistician, will be implemented using the Randomization module within the study database in VA REDCap. The Randomization module within REDCap prevents all users from viewing the treatment assignment of future study participants. This will ensure that all study personnel are blinded to treatment assignment prior to randomizing each participant.

The study coordinator will work with participants individually to ensure technology access and increased comfort level using the virtual platform. Devices and/or internet access will be provided to participants who report this as a barrier to participation. For both the nutrition intervention and contact control groups, we will enroll up to 15 participants into each virtual class cohort and run multiple different group sessions.

We will define successful adherence as completion of > 80% of all class sessions by the majority of participants. Length of time required for each educational session as well as modifications to the sessions will be tracked according to the Core functions and forms framework [35]. The core functions of the nutrition education protocol include 1) each session is led by a trained facilitator, 2) each session follows a standardized lesson plan, 3) each session concludes with question and answer opportunities with participants, and 4) each session is held in a group-based format. The “forms” are the specific ways in which each of the core functions are carried out when implemented under real world conditions and are modified to meet the needs of the local context and participants. For instance, standardized lesson plans may be adapted based on the cultural background of participants, and question and answer opportunities may include questions that are unique to a certain patient population (e.g., people with heart disease). All “forms” will be tracked by the class facilitator during each session to explore how the intervention should be tailored to meet participants needs and inform how other organizations may want to implement our nutrition program in the future.

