#### Contact control group

In the contact control group, virtual live group health education sessions led by staff will be held for one hour/week over 12 weeks. The content for the program was modeled on the “10 Keys to Healthy Aging” curriculum and the National Council on Aging’s “Aging Mastery Program”. Topics focus on a broad range of healthy aging, such as importance of sleep, physical activity, goal setting, self-care, and common comorbidities [38, 39].

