#### Follow up focus groups

Participants randomized to the nutrition intervention who completed all outcome assessments will be invited to participate in focus groups at 6 months. We will complete 3–4 focus groups with ~ 5–8 participants per focus group (total *N* = 20). Sessions will be recorded, transcribed, and coded using qualitative software to identify themes, examine patterns and overlap, and develop a network diagram of interrelationships. Themes will describe correlates of diet quality, social engagement, and technology use that likely influence treatment. To inform future implementation and sustainment, transcripts will also be coded for implementation barriers and facilitators, and mapped to the Consolidated Framework for Implementation Research (CFIR) [55, 56]. These follow-up focus groups will provide key information on sustainability and discern barriers and facilitators to virtual intervention implementation and continued adherence after intervention completion. Key questions for the follow-up focus group include: (1) How did this program influence your ability to move safely around your home?; (2) How did this program influence your social opportunities?; (3) How did this program help you prepare meals at home?

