### Sample size and power

Group sample sizes of 73 in the experimental arm and 73 in the control arm achieve 80.3% power to reject the null hypothesis of equal mean changes in the HEI2015 total score when the population difference in mean change in the two arms is µ1 - µ2 = 5.5 with a standard deviation for both arms of 13.3 and with a significance level (alpha) of 0.05 using a one-sided two-sample equal-variance z-test. The standard deviation is derived based on work from our nonrandomized virtual nutrition education with cooking demonstrations pilot study data. We anticipate enrolling 90 participants per group to achieve this target sample size assuming ~ 20% drop out rate. This drop-out rate is consistent with our previous studies.

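### Continued participation after week 12 is self-selected after randomisation, so testing whether it 'moderates' the persistent effect cannot show effect modification

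*Protocol article*

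**What the plan says.** The last analysis announced in the protocol article's Statistical methods section, before the text on missing data, is this: "we will test whether continued participation in the virtual nutrition intervention after intervention completion moderates the persistent effect" of the intervention on study endpoints. It follows the piecewise modelling of the outcomes and is worded as a test. The label of exploratory post hoc work in that section is attached to the heterogeneity analyses, not to this sentence.

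The design facts that bear on it are these.

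- Randomisation (Intervention): after baseline testing, "participants will be randomized to one of two virtual intervention groups using a 1:1 ratio". No second randomisation is described.
- Nutrition arm (Virtual nutrition education + produce group): weekly one-hour live sessions for 12 weeks.
- Control arm (Contact control group): "virtual live group health education sessions led by staff will be held for one hour/week over 12 weeks". No later offer of the nutrition programme is described.
- After completion: the focus groups are to discuss "barriers and facilitators to virtual intervention implementation and continued adherence after intervention completion". The article describes no nutrition sessions after week 12.
- Follow-up: assessments are repeated at 6 months, three months after the programme ends, and the abstract says "Secondary outcomes include change in HEI from 3 to 6 months".

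**The concern.** A moderator of a randomised effect is ordinarily a characteristic fixed before randomisation, so that within each of its levels the two arms remain comparable. Continuation is not of that kind. It arises after assignment, after 12 weeks of exposure and after the 3-month response has taken shape. The people who continue may be those who responded best, who are in better health or who are more motivated. The article's own Discussion names health problems, caregiving duties, cooking skills and home environment as things that may affect adherence.

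At stake is what the trial may say about persistence. Under the stated wording, a better 6-month score among continuers could be reported as evidence that continuing sustains the benefit, although it may show only who chose to stay. The article presents sustainability as an interest of the trial, so such a result would probably be used.

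**Working it through.** **1. The plan's own figure.** The article gives no number for the continuation analysis. Its only related figure is the power for the 3-month comparison, from 73 per arm, a difference of 5.5 and "with a standard deviation for both arms of 13.3", one-sided at 0.05. SE = 13.3 × √(2/73) = 2.20; 5.5/2.20 = 2.50; 2.50 − 1.645 = 0.85; power ≈ 0.803. This reproduces the stated 80.3% and does not bear on the present point.

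**2. Timing.** Randomisation comes first, then 12 weekly sessions and the 3-month assessment, then continuation or not, then the 6-month assessment. Continuation is therefore a post-randomisation variable, and nothing in the article assigns it. This step needs no assumption about what access is offered after week 12.

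**3. What can be estimated, if no control joins the nutrition programme before 6 months.** Take a model with an intercept, arm (A), continuation (C) and A × C. The article states no model; this one is the usual reading of 'moderates'. The possible rows are:

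| Group | 1 | A | C | A × C |
|---|---|---|---|---|
| Control | 1 | 0 | 0 | 0 |
| Nutrition, stopped | 1 | 1 | 0 | 0 |
| Nutrition, continued | 1 | 1 | 1 | 1 |

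The columns C and A × C are identical, so the matrix has rank 3 with 4 parameters. The one estimable term is nutrition-continued against nutrition-stopped. If some controls were offered the programme, a fourth row (1, 0, 1, 0) would appear and the rank would be 4. Step 2 would still apply.

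**4. Sensitivity to selection (illustration only).** The bias cannot be derived from the document. To show how it behaves, assume that continuing has no effect, that a proportion p of the arm continues, that continuation is decided by a latent trait correlated ρ with HEI change, and that the SD of 13.3 carries over to 6-month change. The expected unadjusted difference is ρ × 13.3 × φ(z)/[p(1 − p)], where φ(z) is the normal density at the cut-off.

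- p = 0.5: φ(z)/[p(1 − p)] = 0.399/0.25 = 1.60
- p = 0.3: 0.348/0.21 = 1.66
- ρ = 0: 0 points
- ρ = 0.2: 0.2 × 13.3 × 1.60 to 1.66 = 4.3 to 4.4 points
- ρ = 0.3: 0.3 × 13.3 × 1.60 to 1.66 = 6.4 to 6.6 points

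Simulation of an arm of 73 under the same assumptions gave the same values to rounding. Both ρ and p are chosen, not known. Adjustment for 3-month HEI removes only the selection that acts through 3-month HEI.

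**5. Precision, a separate matter from bias.** With 73 nutrition-arm completers and the same SD assumption:

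- 36 continue, 37 stop: 1.96 × 13.3 × √(1/36 + 1/37) = 6.1 points
- 22 continue, 51 stop: 1.96 × 13.3 × √(1/22 + 1/51) = 6.6 points
- As randomised, 73 against 73: 1.96 × 2.20 = 4.3 points

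These are unadjusted 95% half-widths. They show that the within-arm contrast is also the less precise one, and they do not measure the selection bias.

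**The case against.** The strongest reply is that this is one sentence in a condensed article. The model, the adjustment set, the definition of continued participation and the handling of self-selection all belong in a statistical analysis plan that is not shown. No interaction term is written down, and an analyst could fit a within-arm continuation term for months 3 to 6 that is fully estimable. The article makes no causal claim about continuing, and the analysis is supplementary.

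Much of this stands. The absence of those details is no fault here. What remains is the stated aim. An analysis plan can add covariates, weighting or principal stratification, but it cannot turn a choice made after week 12 into a baseline moderator. The answer would still rest on assumptions that randomisation does not supply.

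Three stronger readings are tempting and are not supported.

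- A reader might infer that the interaction is impossible whatever the full protocol provides. The Contact control group section says what controls receive for 12 weeks, not what they may be offered afterwards. That only the nutrition arm can continue is an inference from the arm descriptions, so the rank result is conditional.
- A reader might take the figures in step 4 as the bias to expect. They follow entirely from assumed inputs.
- A reader might infer that the sentence is a slip, since no sessions after week 12 are described. The focus-group text also speaks of adherence after completion. That may mean keeping up dietary habits rather than attending sessions, so it settles nothing either way.

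**Conclusion.** The point holds as a minor one. Continuation follows the single randomisation and is self-selected, so a continuer versus non-continuer difference at 6 months is an observational association. It cannot show that continuing modifies or sustains the randomised effect, which is what the word 'moderates' claims. This conclusion rests only on the order of events in the article.

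A second conclusion is conditional: if no control is offered the nutrition programme before 6 months, the arm-by-continuation interaction is not separately estimable, and only the within-arm contrast remains.

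The size of the bias is unknown. A reader might infer that the trial's persistence result as a whole is compromised. It is not: the 6-month comparison of the arms as randomised does not depend on who continued, and neither do the 3-month primary analysis and the sample size.

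**What to change.** Replace the sentence in Statistical methods with:

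> *Within the nutrition arm, we will explore the association of attendance in months 3 to 6 with 6-month outcomes, adjusted for baseline and 3-month values. This analysis is non-randomised and will not be interpreted causally or as moderation of the treatment effect.*

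If no access is offered after week 12, delete the sentence instead. In either case, base claims about persistence only on the as-randomised 6-month comparison. If access is offered, describe that comparison as including it.

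The cost is a change of wording, plus an attendance log for months 3 to 6 if access is offered and attendance is not already recorded. The article already defines adherence by sessions completed ("We will define successful adherence as completion of > 80% of all class sessions by the majority of participants"), although that definition does not itself show that attendance is logged after week 12. A supplementary claim of moderation is given up. The change should be made before the 6-month data are analysed.

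### Five to ten imputations, the only number the article gives, is low for about 20% dropout and leaves a near-threshold primary result dependent on the random seed

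*Protocol article*

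**What the plan says.** Under Statistical methods, the article states: "Missing data will be handled using an intention-to-treat approach with multiple imputations", and continues "with 5–10 imputations recommended to account for uncertainty in missing values". It presents this as giving valid and unbiased treatment-effect estimates and cites a source. It gives no other number of imputations and no limit on Monte Carlo error. The sentence is not confined to secondary outcomes, so it covers the primary HEI outcome.

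Under Sample size and power, the amount of missing data to plan for is given: "We anticipate enrolling 90 participants per group to achieve this target sample size assuming ~ 20% drop out rate". The target is 73 evaluable per arm. The only significance level in the article is there too: "with a significance level (alpha) of 0.05 using a one-sided two-sample equal-variance z-test".

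**The concern.** Multiple imputation draws random values, so the pooled estimate and its p-value change with the seed unless the number of imputations is large. With about a fifth of participants expected to drop out, 5 to 10 imputations leave enough of this noise to matter when the primary result lies near the significance threshold. Two analysts who follow the text on the same data, with different seeds or with different choices inside the 5-to-10 range, could then report different conclusions on the primary outcome. The trial is planned at about 80% power, so a result near the threshold is a realistic prospect.

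**Working it through.** **Inputs from the article (Sample size and power).** 90 enrolled and 73 evaluable per arm; difference in mean change 5.5 HEI points; SD 13.3; one-sided alpha 0.05; stated power 80.3%.

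**Assumptions not in the article.** Data missing at random; imputation model containing arm and at most one covariate, correlated 0 or 0.5 with the change score; primary test a between-arm comparison of change at one-sided 0.05, as in the power calculation. (Statistical methods names a paired t-test; the between-arm reading is taken here.)

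**Step 1: the plan's own figures.** SE = 13.3 × sqrt(2/73) = 2.20. Power = Φ(5.5/2.20 − 1.645) = Φ(2.498 − 1.645) = 80.3%, as stated. Implied missingness is (90 − 73)/90 = 18.9%.

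**Step 2: fraction of missing information.** Simulating 90 per arm with 17 missing per arm gave FMI of about 0.20 with an uninformative covariate and 0.15 to 0.17 with a covariate correlated 0.5. The range 0.15 to 0.25 is used below.

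**Step 3: noise between seeds.** The Monte Carlo SD of the pooled z is about sqrt(FMI/m). At FMI 0.20:
- m = 5: sqrt(0.20/5) = 0.20
- m = 10: sqrt(0.20/10) = 0.14
- m = 50: sqrt(0.20/50) = 0.063

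For a long-run one-sided p of 0.05 (z = 1.645), 95% of runs have z within 1.645 ± 1.96 × SD:

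| m | z range, FMI 0.20 | p range, FMI 0.20 | p range over FMI 0.15–0.25 |
|---|---|---|---|
| 5 | 1.25 to 2.04 | 0.021 to 0.105 | about 0.02 to 0.10–0.11 |
| 10 | 1.37 to 1.92 | 0.027 to 0.086 | 0.025–0.03 to 0.08–0.09 |
| 50 | 1.52 to 1.77 | 0.039 to 0.064 | about 0.04 to 0.06–0.07 |

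**Step 4: fixed datasets, re-imputed.** Each simulated dataset was held fixed and re-imputed 2000 times per m, with proper Bayesian normal imputation, Rubin's rules and Barnard–Rubin degrees of freedom. Share of seeds giving one-sided p ≥ 0.05:

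| Long-run p | m = 5 | m = 10 | m = 50 | m = 100 |
|---|---|---|---|---|
| 0.02 | 5–8% | 0.4–0.9% | 0% | 0% |
| 0.03 | 19–22% | 7–10% | 0% | 0% |
| 0.04 | 34–38% | 25–30% | 4–8% | 1–2% |
| 0.045 | 45–46% | 39–42% | 22–25% | 13–17% |

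**Step 5: whole trials, not only borderline ones.** At the design effect (5.5 points, SD 13.3, 90 per arm with 73 observed), two seeds disagree on significance in about 8–9% of trials at m = 5, 5.5% at m = 10, 3.8% at m = 20 and about 2% at m = 50 to 100. Power is about 77% at m = 5 and 79–80% from m = 10 upwards. Under the null, type I error is 0.046 to 0.049 for every m.

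**The case against.** The strongest reply has four parts.

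- **The article recommends; it does not fix.** It offers a range with a citation, and the final number and seed could be set in the full protocol or SAP, which are not shown. A reader might infer that the trial is committed to 5 or 10 imputations; the wording does not support that. What stands is that 5 to 10 is the only number given, it is low for the expected dropout, and an analyst working from the article would use it.
- **Nothing is invalid.** A reader might infer biased estimates or an inflated false-positive rate. Neither follows: type I error holds at every m. Relative efficiency, 1/(1 + FMI/m), is 1/(1 + 0.20/5) = 96% at m = 5 and 98% at m = 10. That figure and the seed noise are two views of one quantity, since FMI/m is the between-seed variance relative to the total; 96% efficiency and a Monte Carlo SD of 0.20 standard errors are the same fact. High efficiency therefore neither contradicts nor removes the movement of the p-value in a single run.
- **The borderline case exaggerates.** Conditioning on a p exactly at the threshold makes any m look unstable, and even 50 imputations give a range that straddles 0.05. This is fair, and is why the whole-trial rates are given: going from 10 to 50 changes the picture in about 3 trials in 100.
- **The FMI is assumed.** No imputation model is stated, and 20% is a planning allowance for total dropout. Missingness at 3 months may be lower, which would shrink the effect.

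**Conclusion.** The point holds as a minor weakness in reproducibility. The number of imputations recommended is low for the dropout the article expects, and it leaves a near-threshold primary result open to change with the seed. At the design effect, two seeds disagree in about 8–9% of trials with 5 imputations and 5.5% with 10, against about 2% with 50 to 100. Clearly significant and clearly null results are little affected. At the low end of the range there is also a small cost in power, about 77% against 79–80%.

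The figures rest on missing at random, FMI between 0.15 and 0.25, missingness near 19% at 3 months, and a between-arm test at one-sided 0.05. It would go too far to conclude that a larger number removes seed dependence: at a long-run p of 0.045, 13–17% of seeds still cross 0.05 with 100 imputations.

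**What to change.** Replace the recommended range with one pre-specified, larger number of imputations, for example 50 to 100, and state that the seed is set before the analysis. The larger number reduces the noise. The pre-set seed takes away the remaining choice when a result falls very close to the threshold. The exact number within that range is a matter of judgement; a stated limit on Monte Carlo error would be another way to justify it.

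The cost is one sentence and minutes of computing. Enrolment, procedures and participant burden do not change.
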